## Abstract

**Background and aims:**

Cardiac arrest (CA) in children is a major public health problem. Thanks to advances in cardiopulmonary resuscitation (CPR) guidelines and teaching skills, results in children have improved. However, pediatric CA has a very high mortality. In the treatment of in-hospital CA there are still multiple controversies. The objective of this study is to develop a multicenter and international registry of in-hospital pediatric cardiac arrest including the diversity of management in different clinical and social contexts. Participation in this register will enable the evaluation of the diagnosis of CA, CPR and post-resuscitation care and its influence in survival and neurological prognosis.

**Methods:**

An intrahospital CA data recording protocol has been designed following the Utstein model. Database is hosted according to European legislation regarding patient data protection. It is drafted in English and Spanish. Invitation to participate has been sent to Spanish, European and Latinamerican hospitals. Variables included, asses hospital characteristics, the resuscitation team, patient’s demographics and background, CPR, post-resuscitation care, mortality, survival and long-term evolution. Survival at hospital discharge will be evaluated as a primary outcome and survival with good neurological status as a secondary outcome, analyzing the different factors involved in them. The study design is prospective, observational registry of a cohort of pediatric CA.

**Conclusions:**

This study represents the development of a registry of in-hospital CA in childhood. Its development will provide access to CPR data in different hospital settings and will allow the analysis of current controversies in the treatment of pediatric CA and post-resuscitation care. The results may contribute to the development of further international recommendations.

*Trial register*: ClinicalTrials.gov Identifier: NCT04675918. Registered 19 December 2020 – Retrospectively registered, https://clinicaltrials.gov/ct2/show/record/NCT04675918?cond=pediatric+cardiac+arrest&draw=2&rank=10

## Background

Pediatric in-hospital cardiac arrest (IHCA) is a rare event with possible devastating consequences. It is considered a major public healthcare problem. Thanks to advances in cardiopulmonary resuscitation (CPR) guidelines and teaching skills, results in children have improved [1, 2]. However, pediatric CA still has a very high mortality [3–5].

Survival to pediatric IHCA has been related to multiple factors. Previous studies have described the influence of patient characteristics, quality of CPR, post-resuscitation factors and team interventions in mortality [3, 4, 6–8]. Current recommendations on CPR have insisted on the importance of quality and post-resuscitation care in an attempt to improve outcomes [9]. However, in the treatment of in-hospital CA there are still multiple controversies and gaps of knowledge.

### Quality CPR

Some clinical and experimental studies have suggested that quality of cardiopulmonary resuscitation (frequency and depth of chest compressions, compression-decompression ratio, coordination of chest compressions and ventilation with coordination of rescuers) is associated with better CPR results [10].

### Ventilation for pediatric CA

In the last decade, some authors have suggested that initial basic CPR with only chest compressions may be equal to or better than providing chest compressions plus ventilation. In contrast, clinical studies in children [11] and experimental studies in child animal models [12] have shown that early ventilation and oxygenation are essential in child CPR. Intubation during CPR has for many years been considered an essential maneuver during advanced CPR, as it achieves safe isolation of the airway and allows good ventilation. However, intubation is a technique that requires learning and training and can be difficult to perform in emergency situations such as a CA. In recent years, several studies in adults and children have suggested that intubation during CPR is associated with a worse survival and neurological prognosis [13, 14], but a recent large study in adults does not confirm these results [15]. There are no controlled, experimental, descriptive or clinical studies that have looked at this problem.

### Post-resuscitation factors

Once ROSC is achieved, efforts towards survival have to assess and treat post-cardiac arrest syndrome. Outcomes in terms not only of survival, but of good neurological outcome, depend on various factors, including hemodynamics, ventilation and oxygenation, temperature control, sedation and analgesia.

Hypotension after ROSC is associated with a worse prognosis. The ILCOR group recommends keeping systolic blood pressure (BP) above the 5th percentile, but there are no studies that assess which is the best BP in the post-resuscitation period or whether treating low blood pressure influences outcomes [16].

Several studies in adults and children have analyzed the influence of ventilation and oxygenation after ROSC on prognosis. Although the results between all the studies are not in agreement, most suggest that both hypoventilation and hyperventilation are associated with a worse prognosis [17]. Hypoxia can also be a poor prognostic indicator, while the results with hyperoxia are contradictory [16].

Hyperthermia after ROSC is common and is associated with a worse neurological prognosis, which increases with each degree of body temperature above 37 °C. Experimental studies in animals have demonstrated the neuroprotective effect of hypothermia. Initial studies in adults found that hypothermia improved the neurological prognosis in patients recovered from CA. However, the most recent studies in adults and children have found that therapeutic hypothermia is not associated with a better neurological prognosis or longer survival [18]. Therefore, at the present time, strict temperature control and avoiding hyperthermia are recommended.

Sedation and analgesia are fundamental in caring for the critical care child. They enable anxiety and pain treatment as well as shivering control for temperature management. However, after CA its use can difficult neurological assessment, and to date, no study has been able to describe the influence of different analgosedation protocols in neurological outcomes.

### Rational for the study

For the past years, the International Liaison Committee on Resuscitation (ILCOR) has endeavored its efforts in the identification of these gaps of knowledge and their resolution. There are few clinical data to verify the efficacy of CPR interventions in the pediatric population. Thus, the development of collaborative multicenter studies is needed. The objective of this study is to develop a multicenter and international registry of in-hospital pediatric cardiac arrest including the diversity of management in different clinical and social contexts. Participation in this register will enable the evaluation of the diagnosis of CA, CPR and post-resuscitation care and its influence in survival and neurological prognosis.

## Study aims

The objective of PACHIN is (1) to study the relationship between the characteristics of cardiopulmonary resuscitation (CPR) and outcomes, focusing on the influence of ventilation parameters (intubation or not during resuscitation and controlled or uncontrolled ventilation) on the recovery of spontaneous circulation, survival, and short- and long-term neurological prognosis of children with in-hospital cardiac arrest. (2) To study the relationship between post-resuscitation measures (especially ventilation, oxygenation, blood pressure, analgosedation and temperature) with survival and short- and long-term neurological prognosis in children with IHCA. (3) To create a permanent register of pediatric in-hospital cardiac arrest for European and Latinamerican countries.

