## Methods and analysis

### Study design

This study is a multicenter, international, prospective observational registry.

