### Patient elegibility

Inclusion criteria: all children aged 1 month to 18 years who suffer a CA in hospital. For the study, CA is defined as the absence of vital signs requiring at least one minute of chest compressions. Subsequent episodes of CA may be included for the same individual.

Exclusion criteria: Patients being treated with extracorporeal circulatory support (ECMO or ventricular assistance) at the time of CA. Patients who suffer a cardiac arrest and require ECMO for ROSC, after performing conventional CPR, will not be excluded. Duration of the data collection period 24 months.

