### Data collection

Data will be collected, verified, and uploaded to a protected electronic web-based database (Xolomon) by their designated site coordinators/investigators under the oversight of their IRB. Database has been designed following the Utstein model [19]. Database is hosted according to European legislation regarding patient data protection. It is drafted in English and Spanish.

Variables recorded will include hospital characteristics, the resuscitation team, patient’s demographics and background, CPR, post-resuscitation care, mortality, survival and long-term evolution (see Table 1).

**Table 1 Tab1:** Description of variables collected in database

Hospital characteristics: level of care; existence of cardiac arrest management plan; rapid response team: existence and composition; early warning scores
Patient demographics and characteristics: patient data before cardiac arrest (age, sex, weight, height, baseline neurological assessment, medical history, previous treatments)
Description of cardiac arrest: date and time; cause of arrest; place of arrest; cardiac rhythm; contributing factors
Description of cardiopulmonary resuscitation: resuscitation team (team members, number of providers, background); ventilation (airway management, ventilation objectives), chest compressions (rate, depth, synchrony, feedback device); defibrillation (shocks, energy); drugs (adrenaline, amiodarone, lidocaine, calcium, bicarbonate, fluids, others); quality control (invasive blood pressure, end tidal CO2); other treatments (ECMO, POCUS, drainage); time to ROSC; CPR ending; CPR complications; survival; cause of death
Post-resuscitation care: hemodynamic care (blood pressure, drug support, cardiac rhythm); ventilatory support (mechanical ventilation, ventilation parameters, oxygenation, blood gases results); neurological examination (BIS, pupils, Glasgow coma scale, POPC); renal support treatment; metabolic parameters; temperature control management
Outcomes: length of PICU and hospital stay; neurological outcome at discharge (POPC, Glasgow coma scale)
Long term follow-up: brain image (MRI, CT scan, EEG); neurological examination

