### Outcomes assessment

The primary outcome is survival at hospital discharge. Secondary outcome being survival with favorable neurological status. Analysis of different factors influencing both outcomes will be performed.

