### Sample size

As this is an observational study with no intervention, we have not conducted a power calculation. Based on previous studies [3], we estimate that we will enroll at least 250 to 300 eligible cardiac arrest events. This would represent a large international dataset of pediatric cardiac arrest data with significant power to enable exploration of important correlations between performance and survival through multivariate analysis.

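### Aim 1 words intubation as a yes/no exposure during CPR and Table 1 shows no time of intubation, so the comparison is open to resuscitation-time bias, most likely against intubation

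*Protocol article*

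**What the plan says.** All references are to the protocol article.

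- **Study aims:** the first aim relates CPR characteristics to outcome, "focusing on the influence of ventilation parameters (intubation or not during resuscitation and controlled or uncontrolled ventilation) on the recovery of spontaneous circulation". The outcomes are named in full in the same sentence: "on the recovery of spontaneous circulation, survival, and short- and long-term neurological prognosis of children with in-hospital cardiac arrest".
- **Study design:** "This study is a multicenter, international, prospective observational registry". Intubation is therefore not allocated by design.
- **Patient eligibility:** "CA is defined as the absence of vital signs requiring at least one minute of chest compressions". No upper limit on CPR time is given.
- **Data collection, Table 1:** the airway entry reads "ventilation (airway management, ventilation objectives"). Time to ROSC and the end of CPR are listed. A time of intubation and the presence of a tube at arrest are not shown.
- **Outcomes assessment:** "The primary outcome is survival at hospital discharge". Factors related to the outcomes are to be analysed, with no method named.
- **Sample size:** 250 to 300 events are expected, with no power calculation. The only inferential method named in the article is "exploration of important correlations between performance and survival through multivariate analysis".
- **Limitations:** the article accepts that single effects are hard to isolate, but does not mention CPR duration or the timing of the exposure.

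**The concern.** As worded, the exposure is whether a child was intubated at any point in the resuscitation. That can happen only while CPR is still going on. A child with early ROSC has had few minutes in which to be intubated, and a child in prolonged arrest has had many. Group membership therefore depends partly on time to ROSC, which is close to the outcome itself. This is resuscitation-time bias, a form of immortal-time bias.

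The Background says that several studies linked intubation during CPR to worse survival and neurological outcome, that a large adult study did not confirm this, and that the question is open. A yes/no comparison can produce such an association when intubation does nothing. The Discussion expects the results to contribute to international recommendations, so an artefact here would matter. Data collection is prospective, and a time of intubation that was never recorded cannot be restored by a later choice of model.

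**Working it through.** **No figure to reproduce.** The article gives no alpha, power, effect size or event rate. Its 250 to 300 events are a recruitment estimate. Every rate below is an assumption.

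**Mechanism.** Assume intubation times are exponential with median 5 minutes, unrelated to prognosis. The chance of being intubated before CPR ends at minute t is 1 − 0.5^(t/5).
- t = 3: 1 − 0.5^0.6 = 1 − 0.66 = 34%.
- t = 25: 1 − 0.5^5 = 1 − 0.03 = 97%.

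The exposure tracks CPR duration although intubation has no effect.

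**Simulation A, no effect of intubation.** ROSC time is 1 minute plus an exponential with median 12. Termination is 1 minute plus a lognormal with median 30 (log SD 0.5). Intubation has median 5. Survival after ROSC has log-odds ln(0.7/0.3) − 0.05 × minutes of CPR.
- ROSC, intubated vs not: 0.74 vs 0.95. OR = (0.74/0.26)/(0.95/0.05) = 2.85/19 = 0.15.
- Survival: 0.39 vs 0.60, OR 0.42 from unrounded values.
- Matched on the minute of CPR: survival OR 1.01, ROSC rate ratio 1.00.

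**Range under no effect.** Over 72 scenarios (median ROSC 8–20, termination 5–45, intubation 3–10 minutes, slope 0 or 0.05), the yes/no ROSC OR was 0.03 to 0.62 and the survival OR 0.27 to 0.85. With 275 events and two-sided 5% testing, the chance of a false significant survival difference ran from 7% to 98%.

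**Where the bias shrinks or reverses (still no effect).**

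| Assumption | ROSC OR | Survival OR |
|---|---|---|
| Constant termination hazard, survival unrelated to duration | 1.00 | 1.01 |
| Constant termination hazard, survival falls with duration | 1.00–1.02 | 0.68–0.82 |
| Intubation decided within the first minute | 1.01 | 1.01 |
| 30% of attempts stopped within 5 minutes | about 1.7 | 1.04–1.46 |

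**Tube already in place.** If half of the children in the base case of simulation A had a tube at arrest, counting them as intubated gives a survival OR of 0.47. Counting them as not intubated gives 0.69. The classification alone moves the estimate.

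**Simulation B, does adjusting for total duration repair it?** Discrete minutes: intubation hazard 10% per minute from minute 2; ROSC hazard 0.04, 0.06 or 0.09 × 0.96^t; CPR stopped at 25–49 minutes; logit P(survive | ROSC) = 1.1 − 0.06 × minutes. With no effect and overall survival of about 40%, survival was about 26–28% intubated vs 66% not. The OR was about 0.2, and 0.14 to 0.30 over scenarios.

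| Analysis of survival | No effect | Intubation raises the ROSC rate by 50% |
|---|---|---|
| Ever/never OR | 0.14–0.30 | 0.22–0.41 |
| Adjusted for total CPR duration | about 1.0 | 1.00–1.02 |
| Minute-specific risk sets | 0.99–1.02 | 1.20–1.21 |

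Duration adjustment gives about 1 whether or not there is an effect, because a benefit that acts by shortening CPR is conditioned away. The risk-set comparison tells the two cases apart.

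The overall range of 0.14 to 0.85 joins the survival ORs of simulation B (0.14–0.30) and the 72 scenarios (0.27–0.85).

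**The case against.** A reader might infer that the plan fixes intubation as a yes/no covariate. It does not. The aim names an exposure, the analysis section is descriptive, and multivariate analysis is mentioned without a model. A time-dependent analysis could sit in a full protocol or analysis plan that is not shown. This stands, and the point is therefore conditional on how the aim is carried out.

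A reader might also infer that intubation time is not collected. Table 1 is a condensed list that gives no times for drugs or shocks either. The database follows the Utstein model, and its fields are not shown. The airway entry could hold both the time and tube status at arrest. This also stands. All that can be said is that the article does not show them, and that a time left uncollected is lost.

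The strongest reading is that intubation will look harmful. The documents give no intubation or termination times to support that. Under other assumptions the bias disappears or changes sign, as the working shows, and the magnitudes rest wholly on assumed rates.

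Finally, CPR duration is collected and the Limitations concede that effects are hard to isolate. Neither settles the matter. The concession does not name this bias, and adjustment for total duration can hide a true effect.

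**Conclusion.** The point holds in conditional form. Followed as worded, aim 1 contrasts groups whose membership depends on how long CPR lasts. Unless intubation is handled as time-dependent, the result is open to resuscitation-time bias, most likely against intubation. With no true effect, the survival OR was about 0.14 to 0.85 under assumptions in which failed attempts mostly run longer than successful ones. It was 1.01 with first-minute decisions and 1.04 to 1.46 with many early stops. That the direction can change makes a yes/no estimate uninterpretable as an effect, not safe. The mechanism follows from the exposure wording and the eligibility rule. The sizes rest on assumed times and rates and on intubation being unrelated to prognosis, so they show what could happen and do not forecast the registry's result.

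**What to change.** 1. Confirm that the database records, or add to it, the minute of intubation and whether a tube was already in place at arrest. Do this before more events accrue.
2. Leave children already intubated at arrest out of this contrast, and report them separately.
3. Analyse intubation as a time-dependent exposure. At each minute of CPR, compare children intubated in that minute with children still in CPR and not yet intubated, adjusted for pre-arrest and arrest factors. Risk-set matching or time-dependent propensity matching would serve.
4. Do not adjust for total CPR duration in the model meant to estimate the effect of intubation.
5. Label any ever/never comparison as descriptive only, and name resuscitation-time bias in the limitations.

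**Cost:** at most two extra fields, and none if they already exist. Minute-level times recorded around an arrest will sometimes be approximate. The analysable subset will be smaller than the expected 250 to 300 events, so the estimate will be less precise.

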## Methods and analysis

### Study design

This study is a multicenter, international, prospective observational registry.

### Setting

Patients will be enrolled by participating investigators from European and Latinamerican countries. All sites are susceptible of treating pediatric cardiac arrest patients. Participating hospitals differ in levels of care but are all able to submit their data to the study’s database.

### Patient elegibility

Inclusion criteria: all children aged 1 month to 18 years who suffer a CA in hospital. For the study, CA is defined as the absence of vital signs requiring at least one minute of chest compressions. Subsequent episodes of CA may be included for the same individual.

Exclusion criteria: Patients being treated with extracorporeal circulatory support (ECMO or ventricular assistance) at the time of CA. Patients who suffer a cardiac arrest and require ECMO for ROSC, after performing conventional CPR, will not be excluded. Duration of the data collection period 24 months.

### Recruitment

Study candidates will be identified by a study physician, who will explain the study to parents or guardians. Written informed consent will be obtained from parents or guardians prior to inclusion in the study. A CONSORT (Consolidated Standard of Reporting Trials) flow diagram is shown in Fig. 1.

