## Limitations

The main limitation of the study is that patient recruitment cannot be planned because CA is an unexpected sudden event. On the other hand, when CA happens, all attention is driven towards CPR, so it might be difficult to record all data related to the characteristics of CPR while performing it. Another limitation of the study is that the final results of CPR are influenced by many variables and it can be very difficult to differentiate the isolated effect of each factor. Furthermore, recording as many variables as aimed per CA requires a lot of dedication and careful review and supervision of each case by the study coordinator. Being CA a rare event in pediatric patients, it might be difficult to find statistically significant differences in some parameters such as mortality. Thus, the participation of a significant number of hospital centers and collaborating researchers is necessary. This is one of the fundamental reasons for a multicenter study. Finally, the neurological follow-up at one year of some patients will end after the end of the study period.

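### Entry requires prior written parental consent, so inclusion may depend on whether the child survived; survival to discharge could be overstated, and no record of non-included arrests is described to show by how much

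*Protocol article*

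**What the plan says.** All references are to the protocol article.

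- **Patient eligibility.** The population is "all children aged 1 month to 18 years who suffer a CA in hospital". The qualifying event is the arrest itself: "CA is defined as the absence of vital signs requiring at least one minute of chest compressions". Only children already on extracorporeal support are excluded; death is not a ground for exclusion.
- **Recruitment.** "Study candidates will be identified by a study physician, who will explain the study to parents or guardians". Then: "Written informed consent will be obtained from parents or guardians prior to inclusion in the study". The text gives no waiver, no deferred consent and no route for a child who dies before consent is sought.
- **Outcomes assessment.** "The primary outcome is survival at hospital discharge".
- **Data collection, Table 1.** The database has fields for how CPR ended, survival and cause of death, so deaths are meant to be registered.
- **Limitations.** The section notes that "patient recruitment cannot be planned because CA is an unexpected sudden event". It does not mention selection through consent.
- **Sample size.** At least 250 to 300 events are expected, with no power calculation.

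**The concern.** Eligibility is fixed by the arrest, but entry is fixed by a parental signature that normally comes later. By then the child may have died, and the Background describes mortality as very high. The rule as written therefore allows the primary outcome to influence who is in the dataset.

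If families of children who die are approached less often or agree less often, deaths are under-represented and crude survival is too high. A larger sample would not reduce this. Records that were never entered cannot be recovered at analysis unless something was kept about them. The first two study aims relate CPR and post-resuscitation measures to outcome, so it also matters whether such selection carries over to those associations.

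**Working it through.** The article gives no survival or consent figure, so there is no stated result to reproduce. Survival and consent rates below are assumptions; only the 250 to 300 events come from the article (Sample size).

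**1. Crude survival.** Let S be true survival to discharge, cs the proportion of survivors included and cd the proportion of non-survivors included.

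Observed survival = S·cs / [S·cs + (1 − S)·cd]. Equivalently, the odds of survival are multiplied by cs/cd.

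With S = 0.40:

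| cs / cd | Calculation | Observed | Bias (points) | Odds multiplied by |
|---|---|---|---|---|
| 0.95 / 0.85 | 0.380 / (0.380 + 0.510) | 42.7% | 2.7 | 1.12 |
| 0.95 / 0.70 | 0.380 / (0.380 + 0.420) | 47.5% | 7.5 | 1.36 |
| 0.90 / 0.60 | 0.360 / (0.360 + 0.360) | 50.0% | 10.0 | 1.50 |
| 0.90 / 0.90 | 0.360 / (0.360 + 0.540) | 40.0% | 0 | 1.00 |

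**2. Against sampling error.** Half-width of the 95% interval = 1.96·√[S(1 − S)/n].

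- n = 250: 1.96·√(0.24/250) = 6.1 points.
- n = 300: 1.96·√(0.24/300) = 5.5 points.

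The mildest scenario gives about half of this; the other two exceed it.

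**3. Sensitivity to the assumed survival.** With cs = 0.90 and cd = 0.70, observed survival is 35.5%, 46.2%, 56.25% and 65.9% for S = 0.30, 0.40, 0.50 and 0.60. The bias is 5.5 to 6.25 points, against half-widths of 5.2 to 6.2 points over the same range. A 20-point consent gap thus produces a bias about as large as the sampling error, whichever of these survival levels is true.

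**4. Associations.** With subscripts 1 (exposed) and 0 (unexposed):

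Observed odds ratio = true odds ratio × (cs1/cd1) / (cs0/cd0).

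- *Consent depends on survival alone.* The multiplier is 1. With survival 0.35 exposed and 0.50 unexposed, and consent 0.90/0.50, the odds ratio is 0.538 before and after selection. Observed survival becomes 0.492 and 0.643. The risk ratio moves from 0.70 to 0.77; the risk difference happens to stay close, at −0.150 and −0.151.
- *Consent after death also differs by exposure.* With survivors at 0.90 and deaths at 0.40 exposed and 0.60 unexposed, the multiplier is (0.90/0.40)/(0.90/0.60) = 1.50. A true odds ratio of 1.00 becomes 1.50, and 0.538 becomes 0.808.
- *A route by which this could arise.* Suppose ROSC is 60% exposed and 80% unexposed, survival given ROSC is 50%, and consent is 0.9 for survivors, 0.8 for deaths after ROSC and 0.5 for deaths without ROSC. The true odds ratio is (0.30/0.70)/(0.40/0.60) = 0.64. The observed one is [0.27/(0.24 + 0.20)] / [0.36/(0.32 + 0.10)] = 0.72.

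**The case against.** **No one is excluded for dying.** Bereaved parents can consent and the database has fields for death. This stands: selection is partial, and a reader who inferred that the registry is bound to be a survivors' sample would go beyond the text. The upward direction also rests on lower consent after death, which is plausible but not documented.

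**The size is illustrative.** This stands too. The mildest scenario is smaller than the sampling error. The half-width also treats events as independent, although repeat arrests in one child are allowed, so random error may be somewhat larger than shown.

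**Associations need not be biased.** A reader might infer that losing mainly failed resuscitations distorts every association with survival. That does not follow. If inclusion depends on survival alone, the survival odds ratio is unchanged; distortion needs inclusion that varies with exposure as well as outcome. Differing ROSC rates offer a route to this, but nothing in the article shows that it operates.

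**Country differences.** A reader might also expect consent practice to pass for differences in survival between countries. No such comparison is among the study aims, so this is not part of the point.

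**A condensed article may omit a waiver that the full protocol contains.** Possibly; sites work under their own IRBs, and the flow diagram cannot be seen here. But the point is not a missing detail. The article states a consent rule without exception, and that rule does not fit the stated target of all children. If a waiver or another route exists, the Recruitment text needs correcting.

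**Conclusion.** The point holds as a risk built into the design. Following the Recruitment rule as written lets entry depend on the primary outcome, and nothing in the article allows the effect to be measured or corrected.

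With true survival of 40% and the consent gaps assumed above, survival would be overstated by 2.7 to 10.0 points, against a half-width of about 5.5 to 6.1 points. With equal inclusion of survivors and non-survivors the bias is zero. These figures show what consent gaps of 10 to 30 points would do; they do not predict this registry's result.

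For associations the conclusion is narrower. Survival odds ratios are at risk only if inclusion given outcome also differs by exposure. When a true association exists, risk ratios, and in general risk differences, can shift even under selection on survival alone, though the risk difference barely moved in the example.

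**What to change.** **Log.** At every site, keep an anonymous log of each eligible arrest not included: age band, location, ROSC yes/no, alive at discharge yes/no, reason for non-inclusion and, where permitted, the main exposure, such as intubation during CPR. Without an exposure field the log can correct crude survival but cannot address exposure-dependent consent.

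**Reporting and analysis.**
- Report survival among all eligible arrests alongside survival among consented arrests.
- Give the inclusion rate separately for survivors and non-survivors.
- Use the log for a bounding sensitivity analysis. For odds ratios, the multiplier in step 4 of the working can be varied over the range that the logged rates support.
- Add consent-related selection to the Limitations, and reconcile Patient eligibility with Recruitment by stating how a death before consent is handled.

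**Optional.** Where ethics committees allow it, seek a waiver or deferred consent for routinely collected data. The investigators cannot simply write this in. The study was registered retrospectively, so enrolment may already have begun; any change should therefore be flagged by site and period, so that two ascertainment regimes are not mixed unnoticed.

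**Cost.** A few log fields per non-included arrest, local approval of the log where required, and possibly a less favourable survival figure. The optional route needs an ethics amendment at each site that takes it.
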